### Sample size calculation

The sample size calculation is based on the AST peak, the most important primary endpoint in this trial. According to historic data of about 450 liver transplant recipients at the Department of Surgery, University of Heidelberg, a log-normal distribution of the AST peaks is plausible with a standard deviation of 1.01 for the log (AST peak)-values (details are available on request). These data served for the sample size calculation of this trial. A decreased AST-peak by 300 U/L is considered clinically relevant. Thus a sample size of 65 patients per group, i.e. a total of 130 patients, is sufficient to detect differences with a power of 80%, taking into account the planned interim analysis (two-sided t-test for the log (AST peaks), overall level of significance α = 0.05) (nQuery^® ^4.0, EaSt^®^-2000). Details on transformation of the clinically relevant difference on the original scale to a clinically relevant difference on the log scale used for sample size calculation are available on request.

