### Statistics and data management

All findings including both the clinical and laboratory findings are documented in the subject's case report form (CRF). All data are entered in a database as recorded. To ensure highest data quality a double data entry is performed. All missing data or inconsistencies are reported back to the center(s) and clarified by the responsible investigator. If no further corrections of the database are to be made it will be declared closed and used for statistical analysis.

The primary endpoints of the trial are peak serum levels of both AST and ALT measured within the first 8 days after transplantation, and graft survival based on patients death or announcement for re-transplantation.

Therefore the statistical hypotheses to be tested are as follows:

H0: AST_glycine _= AST_placebo _vs. H1: AST_glycine _≠ AST_placebo_,     (1)

H0: ALT_glycine _= ALT_placebo _vs. H1: ALT_glycine _≠ ALT_placebo_,     (2)

H0: S_glycine _= S_placebo _vs. H1: S_glycine _≠ S_placebo_,    (3)

While AST_glycine _and AST_placebo _represent the distribution of AST peaks in the glycine and placebo group, respectively, ALT_glycine _and ALT_placebo _represent the distribution of ALT peaks in the two groups, and S_glycine _and S_placebo _represent the survival functions of the two groups regarding graft survival.

The statistical hypotheses formulated above will be tested, each at the level of significance α (see below), in the strict order (1), (2), (3), i.e. a statistical testing procedure with a priori ordered hypotheses is applied [41].

All analyses are done according to the principle of intention-to-treat. Additional analyses (per protocol population, sensitivity analyses) will be described in the statistical analysis plan in more detail before closure of the database.

In the interim analysis only safety parameters and the primary endpoints AST peak and ALT peak will be evaluated. Data for the third primary endpoint (graft survival) are collected only at the end of the trial. The interim analysis is performed according to the group sequential design of O'Brien and Fleming [42]. The overall level of significance is α = 0.05, i.e. the level of significance for the interim analysis is α 1 = 0.0035, the level of significance for the final analysis is α2 = 0.0488.

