If a patient dies or a re-transplantation has to be performed during the clinical period, serum measurements are not available. As this is the worst possible outcome, patients will be allocated the worst ranks for the respective (non-parametric) analyses.

Sensitivity analyses regarding the methods for dealing with missing values will be performed. Further details regarding the handling of missing data will be laid down in the statistical analysis plan that will be completed before unblinding of the data.

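### The stated 80% power belongs to a t-test on log AST peaks, but the plan's rule for early deaths and re-transplantations calls for a worst-rank test, for which 80% has not been shown

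*Protocol article*

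**What the plan says.** The section on sample size calculation rests the trial on AST peak, the first of the ordered primary endpoints. It assumes "a standard deviation of 1.01 for the log (AST peak)-values", sets the target by "A decreased AST-peak by 300 U/L is considered clinically relevant", and concludes that "a sample size of 65 patients per group, i.e. a total of 130 patients" is "sufficient to detect differences with a power of 80" per cent. The power is for a "two-sided t-test for the log (AST peaks), overall level of significance α = 0.05", with the interim analysis taken into account. The log-scale equivalent of 300 U/L is not printed; the details of "a clinically relevant difference on the log scale used for sample size calculation are available on request".

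The section on statistics and data management states the AST and ALT hypotheses as equality of distributions between arms and names no test for them. It tests AST, ALT and graft survival in strict order, at two-sided levels of 0.0035 (interim) and 0.0488 (final). It also says "All analyses are done according to the principle of intention-to-treat". For death or re-transplantation during the clinical period it gives one rule: "patients will be allocated the worst ranks for the respective (non-parametric) analyses". Sensitivity analyses for missing values come after that rule, as something separate.

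**The concern.** The power statement and the rule for early losses rest on different tests. A patient with a worst rank has a position in an ordering but no log AST value, so the t-test cannot use that patient. Under intention-to-treat the patient stays in the analysis. The test that carries out the rule is therefore a rank test on all randomised patients, and the protocol gives no power for it.

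Two losses could follow, and the sample size section allows for neither. A rank test is slightly less efficient than a t-test when log values are normal. Patients tied at the worst rank in both arms also dilute the AST shift that the trial was sized to detect.

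AST is the gatekeeper. If it is not significant, neither ALT nor graft survival can be tested, and the article describes graft survival as the endpoint that reflects possible clinical benefit. A t-test in one section and a non-parametric rule in another, with no stated choice between them, also leaves the key analysis open longer than it should be.

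**Working it through.** **Inputs from the protocol article:** 65 per group, 1:1; SD 1.01 on the log scale; 80% power; final level 0.0488 and interim level 0.0035, both two-sided. **Not given, so assumed:** the log-scale difference, the early-loss rate per arm, and an interim look at about half the patients.

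**1. The plan's own figure.** The 65 per group cannot be reproduced forwards, because the log-scale difference is missing. Solved backwards with a noncentral t distribution:

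- Noncentrality = (δ/1.01) × √(65/2). With 128 degrees of freedom the critical value at 0.0488 is 1.989.
- 80% power needs δ = 0.502, since 0.502/1.01 = 0.497 and 0.497 × 5.701 = 2.83.
- Ratio of geometric means = exp(−0.502) = 0.605, about 39% lower.
- If 300 U/L is a difference in medians, the placebo median is 300/(1 − 0.605) ≈ 760 U/L.

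This is circular by construction. It shows the effect at which the 80% would be true, not that the plan used that effect. The two levels are sound: together they give an overall error of 0.0500 with the interim at half the information.

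**2. The rank test, approximate formula.** Without losses, P(placebo peak > glycine peak) = Φ(0.502/(1.01 × √2)) = Φ(0.351) = 0.637. With losses p_P (placebo) and p_G (glycine), independent of AST and tied at the worst rank:

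θ = p_P(1 − p_G) + ½ p_P p_G + (1 − p_P)(1 − p_G) × 0.637

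Power ≈ Φ[(θ − 0.5) × √(12 × 130 × ¼) − 1.970], where the root is √390 = 19.75.

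- No losses: 0.137 × 19.75 = 2.71; 2.71 − 1.97 = 0.74; power 0.77.
- Equal loss p in both arms: the formula reduces to 0.137 × (1 − p)². For p = 5% that is 2.71 × 0.9025 = 2.45; 2.45 − 1.97 = 0.48; power 0.68.
- 10% v 5%: θ = 0.095 + 0.0025 + 0.855 × 0.637 = 0.642; 0.142 × 19.75 = 2.81; power 0.80.

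**3. Simulation.** Unstratified Wilcoxon test with tie-corrected variance, 65 per group, log difference 0.502, level 0.0488. Counting the interim look changes the results by at most 0.2 points.

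| Early loss, placebo v glycine | Power |
|---|---|
| None | 78% |
| 2% v 2% | 75% |
| 3% v 3% | 73% |
| 5% v 5% | 69% |
| 10% v 10% | 59% |
| 5% v 2.5% | 79% |
| 8% v 4% | 80% |
| 10% v 5% | 81% |
| 10% v 2% | 90% |
| 5% v 8% | 55% |

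With no losses, about 68 per group would restore 80%, so the change of test alone is worth about three patients per group.

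**4. Loss that follows AST.** Here the chance of early loss rises with the patient's underlying log AST, by one logistic model in both arms with an assumed slope of 1 to 3 per SD. Power is then 77-78% at 3% placebo loss, 76-78% at 5% and 72-77% at 10%. Patients lost for this reason would mostly have ranked near the worst anyway, and placebo loses more of them. With slope zero the same model returns the 69% and 59% in the table.

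**5. Sensitivity to the back-solved effect.** If the t-test in fact had 83% power at 65 per group (log difference 0.522), the rank test would have about 82% without losses, 73% with 5% equal loss and 63% with 10%.

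**The case against.** A reader might infer that the trial is underpowered, or that the worst-rank test cannot have 80% power with 65 per group. The documents do not support that. The article says only that 65 is sufficient, prints no log-scale effect and gives no early-loss rate. The change of test alone costs about 2 points. The largest shortfalls need equal loss in both arms that is also unrelated to AST, which sits badly with the article's own statement that rising transaminases go with primary organ failure. If glycine reduces early loss, as the trial hopes, power is near or above 80%. All of this stands, and it limits the point to a figure that has not been shown.

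A reader might also infer that early losses will be dropped, against intention-to-treat. Nothing in the plan says so; the worst-rank rule keeps them in.

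It can further be said that the t-test appears only in the sample size section, that hypotheses about distributions suit a rank test, and that the exact test belongs in the analysis plan. The first two are fair, and they favour reading the rank test as the intended one. The third does not remove the point. The article already fixes a power figure for one test and a rule that needs another, and an analysis plan cannot make the printed 80% apply to a test for which it was not computed.

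**Conclusion.** The point holds as a mismatch between the powered test and the test that the plan's own rule requires. The 80% has not been shown for the worst-rank analysis, and no allowance is made for early losses.

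The size is conditional on two things the article does not give: a log difference of about 0.50, back-solved from the stated power, and the early-loss rates. Without losses the shortfall is about 2 points. When loss follows AST it is about 2 to 8 points for placebo loss of 3-10%. It reaches 7, 11 and 21 points only if 3%, 5% and 10% are lost in both arms independently of AST, and it is larger if loss is more frequent on glycine (55% at 5% v 8%). It all but vanishes if glycine halves a 5-10% loss. All figures are for an unstratified test, whereas randomisation is stratified by centre and cold ischaemia time.

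No error-rate problem follows: the interim and final levels are consistent with an overall 0.05. What is at stake is a correct power statement, and a single pre-specified test, for the hypothesis that controls access to the other two.

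**What to change.** Before unblinding, in the protocol and the analysis plan:

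- Name the worst-rank Wilcoxon test as the single primary test for AST peak and for ALT peak, at both the interim and the final analysis.
- Keep the t-test on measured log peaks as a sensitivity analysis.
- Keep 130 patients, and restate power for the test actually named. If that test is stratified, recompute; the figures above do not carry over unchanged.
- Print the log-scale difference, or the ratio, beside the 300 U/L, with the reference AST level that links them.
- Give power over a range of assumed early-loss rates per arm, including equal loss, loss related to AST, and lower loss on glycine, and label these rates as assumptions.

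The cost is wording and a short recalculation, with no extra patients. The article reports about 69 of 130 patients included by June 2005 and an analysis plan still to be completed before unblinding, so the change fits the plan's own timetable. The downside is a power figure that is conditional and, in most scenarios, slightly less favourable than a flat 80%.

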### Randomization and treatment

Here a 1:1 randomization ratio has been chosen. Randomization is stratified for each center and for the duration of cold ischemia (≤ 10 hrs or >10 hrs). The study medication is produced, labeled, and packed by a Clinical Pharmacy Department. The guideline for good manufacturing practice (GMP) is adhered to. The intravenous medication for the verum group contains 250 ml glycine solution (4.4%; 11 g glycine, dissolved in aqua ad injectione). In contrast the placebo consisted of 250 mL of the vehicle (aqua ad injectionem) have to be infused to patients.

All patients receive their first study medication via a central venous line during liver transplantation one hour prior to reperfusion. During the following week, on post operative days (POD) 1 to 7, the study medication is infused once per day in the morning, after taking blood and urine samples for safety and efficacy parameters. A last visit is scheduled for POD 8 to investigate the patients' clinical status and to collect all parameters for efficacy and safety. To detect late graft failures all patients are observed after the initial first eight days until the last patient is enrolled in this trial. These patients will then be observed for at least 31 days after transplantation. A late graft failure is defined as patients' death or announcement for re-transplantation.

If it is medically imperative to know the patient's treatment, emergency envelopes contain the information on the subject's study medication. Those are to be opened only under emergency circumstances. During the trial a concomitant treatment may be given at the discretion of the investigator, if these are considered necessary for the subject's welfare.

All patients routinely receive standard immunosuppressive therapy. The initial dose of CyA is 2 × 2 mg/kg body weight during the first 24 hrs. Subsequently, daily doses of CyA are adapted to the actual CyA serum level which is measured in the blood samples taken in the morning of POD 1 to 8. The trough concentration should be between 200–250 μg/L during the first month after liver transplantation. In case of renal insufficiency FK506 can be used alternatively.

The amount of coagulation factors and AT III, red blood cells, and fresh frozen plasma given after transplantation are documented until the morning of POD 8.

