## Methods / design

After the positive vote of the ethics committee of all involved study sites, enrollment of 130 subjects scheduled for liver transplantation was started in this multicenter, prospective, placebo-controlled, double-blind, randomized clinical trial with two parallel treatment groups (verum / placebo). Only patients who meet all inclusion and exclusion criteria (Table 1) are considered for uptake into the study. Since its initiation in May 2003, about 69 patients have been included until June 2005.

**Table 1 T1:** Criteria of inclusion and exclusion of patients.

Inclusion Criteria	Exclusion Criteria
Patients meeting all of the following criteria are considered for inclusion in the study:	Patients presenting with any of the following are not be included in the trial:
- men and women between 18 and 65 years of age,	- pregnant or nursing women,
- scheduled for first liver transplantation and graft (dead body) already available,	- history of hypersensitivity to glycine or to drugs with a similar chemical structure (amino acids, e.g. serine, threonine, or methionine),
- written informed consent.	- mental conditions rendering the subject incapable to understand the nature, scope, and consequences of the trial,
	- participation in another clinical trial.
	No subject will be enrolled in this study more than once.

Patients are treated for a total of 8 consecutive days (day of transplantation and the seven following days). Subsequently, all patients are observed for an additional follow-up period of at least 23 days. Thus every patient is observed for at least one month (Figure 1). In detail, to assess the incidence of a late onset of graft failure based on patients' death or patients' announcement for re-transplantation all patients will be followed-up until one month after the last patient is randomized for this trial. Patients' status will be obtained via phone interview of the patients' general practitioner and / or the responsible transplant consulting office. The Schedule for all study related activities and data collection is listed in Table 2.

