**Figure 1 F1:**
[figure not shown]
***Scheme depicting the work flow of the study***. After giving informed consent liver transplant recipients are randomized to two parallel groups treated for eight days (day of surgery and the following seven days) using glycine solution or placebo. Follow-up period will be at least 31 days after transplantation.

**Table 2 T2:** Schedule of study related activities and data collection. The following study related activities are planned for each subject. Blood samples already taken in the routine process at the planned time do not have to be taken twice.

	**Clinical period**						**Follow-up period**
**Study related activity**	**pre-OP**	**OP**	**ICU-entry**	**POD 1**	**POD 2–7**	**POD 8**	

Informed consent	**x**						
Medical history	**x**						
Physical examination	**x**						
Donor and graft history		**x**					
Randomisation		**x**					
Treatment		**x**		**x**	**x**		
**Safety parameters **(measured after 5 a.m. before additional treatment, unless otherwise stipulated)							
12-lead ECG	**x**					**x**	
Vital signs	**x**		**x**	**x**	**x**	**x**	
Blood chemistry	**x**		**x**	**x**	**x**	**x**	
Haematological parameters	**x**		**x**	**x**	**x**	**x**	
Coagulation parameters	**x**		**x**	**x**	**x**	**x**	
CyA (trough concentration)				**x**	**x**	**x**	
Pregnancy testing	**x**						
**Efficacy Parameters **(measured after 5 a.m. before additional treatment, unless otherwise stipulated)							
Biopsy		x	(immediately after rearterialisation)				
Blood flow in portal vein and common hepatic artery		x	(1 hour after reperfusion)				
AST, ALT	x		x#	x#	x	x	
Biltotal, Bildir, Quick, AT III	x		x	x	x	x	
Gly*		x			x (POD3)		
KreaS, HS	x		x	x	x	x	
24-hours-urine (VolU, KreaU)				start	x	x	
Indicators for early onset of graft failure				x	x	x	
Occurrence of late onset of graft failure							X

^#^; AST and ALT will be measured every 4 to 6 hours during the first 24 hours after ICU entry.

*; Samples for glycine plasma level has to be collected immediately after first study drug application during surgery and on POD 3 (after study drug application).

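### The placebo is 250 mL of solute-free water for injection, infused eight times: an avoidable haemolysis risk to control patients, with a possible but unquantified tilt of early AST in glycine's favour

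*Protocol article*

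**What the plan says.** All of the following is in the protocol article.

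- **Verum** (Randomization and treatment): "250 ml glycine solution (4.4%; 11 g glycine, dissolved in aqua ad injectione".
- **Placebo** (same section): "In contrast the placebo consisted of 250 mL of the vehicle (aqua ad injectionem) have to be infused to patients". No salt, sugar or other tonicity agent is named.
- **First dose** (same section): "All patients receive their first study medication via a central venous line during liver transplantation one hour prior to reperfusion".
- **Later doses** (same section): "on post operative days (POD) 1 to 7, the study medication is infused once per day in the morning, after taking blood and urine samples". The section gives no infusion rate, and it names a central line for the first dose only.
- **Duration** (Methods / design): treatment covers the day of surgery and the next seven days, so eight doses.
- **Endpoint** (Objectives and endpoints): peak AST from ICU entry through day 8 ranks first among the ordered primary endpoints. Bilirubin AUC and renal retention AUC are secondary.
- **Sampling** (footnote to Table 2): "AST and ALT will be measured every 4 to 6 hours during the first 24 hours after ICU entry".
- **Accrual** (Methods / design): "about 69 patients have been included until June 2005", out of 130 planned.

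**The concern.** Using the vehicle as placebo is normal practice. The difficulty is this particular vehicle: once the glycine is left out, what remains is water with no osmotic content. A fluid of zero osmolality infused into blood can lyse red cells. Only the control arm is exposed, and controls gain nothing from it, because an isotonic solution would blind the trial equally well. These are liver transplant recipients whose renal function is itself under study.

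The second issue is direction of bias. Red cells contain AST, so lysis would push AST up in controls only. Peak AST is the first hypothesis in the ordered testing sequence, and a rejection there opens the tests of ALT and graft survival. Bilirubin and retention values could move the same way.

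Detection is weakened by the rule under Adverse events that events related to the transplant procedure are not recorded unless the investigator attributes them to study drug. After this operation, a fall in haemoglobin or a rise in bilirubin is easily attributed to surgery.

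**Working it through.** **1. Composition.** The stated strength reproduces: 11 g / 250 mL = 4.4%. With a molar mass of 75.07 g/mol for glycine, 11 / 75.07 = 146.5 mmol, and 146.5 / 0.25 L = 586 mmol/L. Placebo as written: 0 mmol/L.

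**2. Exposure per control patient.** 8 doses × 250 mL = 2,000 mL of solute-free water.

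**3. Avoidable exposure.** 130 − 69 = 61 patients remaining in June 2005. At 1:1 allocation, 61 / 2 = 30.5 controls, and 30.5 × 8 = 244 infusions. This is an upper bound, because accrual continues while an amendment is prepared.

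**4. Which AST samples are exposed.** The intra-operative dose precedes ICU entry. The next 24 hours bring 24/6 = 4 to 24/4 = 6 serial samples, and the POD 1 dose may also fall inside that window. From POD 2 the scheduled sample comes before that day's dose, about 24 hours after the previous one. Exposure is therefore concentrated in the first window, and the peak is affected mainly in patients whose highest value falls there.

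**5. Size of an AST shift (illustration on assumed inputs).** The document gives no infusion rate, lysed volume, red-cell AST content or distribution of peak times, so the size cannot be derived. For scale only:

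- From the document: SD of log peak AST 1.01, 65 per arm, 80% power, two-sided 0.05. SE = 1.01 × √(2/65) = 0.177. The detectable log difference is about 0.50 (t-test), a ratio of 0.606.
- Assumption: the 300 U/L target is a reduction from the placebo median. That median is then 300 / (1 − 0.606), about 762 U/L.
- Assumption: lysis adds a constant b U/L to every control peak, with log-normal peaks. The mean log shift is E[ln(1 + b/Y)], where Y is the peak without lysis.

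| Assumed b (U/L) | Mean log shift | Share of 0.50 |
|---|---|---|
| 10 | 0.021 | 4% |
| 20 | 0.042 | 8% |
| 50 | 0.097 | 19% |

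For a given b these overstate the shift, because by step 4 not every control peak is exposed.

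**6. What by-period results could show after a change.** With 69 patients before and 61 after: SE = 1.01 × √(4/69) = 0.243 and 1.01 × √(4/61) = 0.259. The SE of their difference is √(0.243² + 0.259²) = 0.355. That is too imprecise for anything but description.

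**The case against.** **Safeguards exist.** Ethics committees at all sites approved the trial and a pharmacy working to GMP made the product. Table 2 schedules haematology at ICU entry and daily to POD 8, red-cell use is documented, and a safety board operates. The interim look also covers safety: "In the interim analysis only safety parameters and the primary endpoints AST peak and ALT peak will be evaluated". This stands in part. Gross lysis would probably be noticed. A small AST shift would not, and monitoring does not justify a hazard with no purpose.

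**Rate and dilution matter.** Slow infusion through a central line lowers the risk, and an article commonly leaves infusion rate to the full protocol. That is fair, and the absence of a rate is not criticised here. The point rests on the composition that the article does state.

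**The bias has no data behind it.** This largely stands. The direction is sound, but the amount is conjecture. A reader might infer that the water placebo could by itself produce a positive AST result, or that a specific inflation of the type I error can be quoted. The document supports neither: any such probability would be driven by an assumed AST increment and an assumed share of exposed peaks. Nor does the document show that haemolysis occurred.

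**A mid-trial change is untidy.** True. A reader might also infer that adjusting for formulation period would repair the pooled comparison. It would not: period is calendar time shared by both arms, so the earlier glycine-versus-water contrast stays inside the pooled effect.

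**Conclusion.** The point holds, led by patient safety, and should be fixed. It rests on the article's stated composition and on the general fact that solute-free water can lyse red cells. It does not rest on missing detail.

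The AST bias is secondary. Its direction favours glycine, but its size is not derivable and is probably modest; under the assumed increments shown, it stays well below the difference the trial is powered to detect. ALT and graft survival appear less exposed. Possible effects on bilirubin and renal values are not quantified. The confidence is medium, because the infusion rate and the product actually used are not visible in the article.

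**What to change.** For patients still to be randomised, amend Randomization and treatment along these lines:

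> *Placebo is 250 mL of an isotonic, glycine-free solution (for example 0.9% sodium chloride), identical to verum in container and appearance.*

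A salt-free isotonic solution is an alternative if sodium is a concern. Take the decision without unblinded data. This removes the hypotonic load but does not match verum's osmolality: against saline at 308 mOsm/L, a gap of 586 − 308 = 278 mOsm/L remains.

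In addition:

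- Record which placebo formulation was in use for each patient.
- Report AST and ALT effects by formulation period, descriptively only.
- Report haemoglobin and red-cell transfusion by arm from data already being collected.
- State the water placebo as a limitation for patients already treated.

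If the product actually infused was tonicity-adjusted, correct the description instead; no other change is then needed.

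**Cost.** One amendment with ethics approval at all sites, one new placebo batch and no additional patients. The trial would carry two control formulations. Saline brings 0.25 L × 154 mmol/L = 38.5 mmol sodium per dose, or 308 mmol over eight doses.
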